### Sample size and power

The primary focus of Aim 1 is to test the main effect of RUBIES (RUBIES + HELM and RUBIES only) vs. educator psychoeducation on change in children’s externalizing behavior from Baseline to Week 24. Assuming a Type-I error rate of 5% and SD of 6.2, a conservative within-person correlation in externalizing behavior of r = 0.3, 10% intraclass correlation (clustering within schools) for variance inflation and 20% attrition rate in children, a total of 126 autistic children paired 1:1 with educators (84 autistic children for RUBIES + HELM and RUBIES only vs. 42 children in educator psychoeducation) nested within 42 schools are needed to detect a difference of at least 3.8 points in the comparison of slopes in ABC-I with 80% power. A difference of 3.8 corresponds to a moderate standardized effect size of d = 0.62 in between groups change in children’s externalizing behavior and this effect size is clinically meaningful based on prior research [16]. The study assumed a modest clustering within schools of 10% because of the 1:1 pairing of the educator and autistic child. We expect 3 child-educator dyads per school to consent and enroll in the study. Hence, a total of 126/3 = 42 schools are needed.

For Aim 2, we will use only educators in the RUBIES + HELM vs. RUBIES only (84 educators within 28 schools) arms. With 84 educators as the effective sample size (42 each), nested within 28 schools, we have 80% power to detect a difference of at least 0.13 (or d = 0.76) in RUBIES sustainment (Week 52 and Week 76) between RUBIES + HELM vs. RUBIES only assuming SD = 0.17 based on pilot RUBIES data, a Type-I error rate of 0.05, 10% variance inflation for clustering within school effect, 25% attrition rate and within-person correlation of observations = 0.3. We assumed a higher attrition rate for educators since the turnover rate for educators are higher post pandemic.

For Aim 3, we focused the power calculation for the mediation aim on the effects of RUBIES on the hypothesized mediator, children’s self-management skills, in order to establish the discriminant effects of RUBIES relative to educator psychoeducation. Based on Heath et al., [68] children’s self-management skills have a moderately large effect for decreasing challenging behaviors (mediator on outcome). While we do not have preliminary data for the relationship between RUBIES on self-management skills, the power calculation is presented assuming small (0.25) and moderate (0.5) effects of RUBIES on self-management skills (treatment on mediator). With an effective sample size of 126 autistic children nested within 42 schools, we have 67% and 99% power to detect an indirect effect of RUBIES on children’s externalizing behavior assuming 1) small and moderate effects of RUBIES on self-management skills, respectively; 2) a moderate effect of self-management skills on decreasing externalizing behaviors; [68] 3) smaller effect of RUBIES on children’s externalizing behavior (Aim 1; treatment on outcome); and 4) Type I error rate of 0.05.

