#### Clinical outcomes

Student externalizing behavior will be rated at clinical baseline, Weeks 16, and 24. The Sutter Eyberg Student Behavior Inventory-Revised (SESBI-R; primary clinical effectiveness outcome) [43] is an educator-reported measure used to assess conduct problems in youth ages 2–16. It contains 38 items on which teachers indicate the current frequency of behavior problems (Never to Always) and indicate whether or not they find the behaviors problematic. The Intensity and Problem scales of the SESBI-R have demonstrated internal consistency coefficients of 0.98 and 0.96 and test–retest correlations of 0.87 and 0.93, respectively [48].

The Emotion Dysregulation Inventory [44] (EDI, secondary clinical effectiveness outcome) is a questionnaire that assesses emotion regulation and is validated for autistic youth. Educators rate the youth’s observed functioning over the past 7 days using a 5-point Likert scale from “not at all” to “very severe.” The EDI has excellent internal consistency (Cronbach’s alpha > 0.90) [49].

The Aberrant Behavior Checklist [50, 51] (ABC)-Irritability Subscale (secondary clinical effectiveness outcome) measures behavioral challenges in individuals with developmental disabilities. Educators rate items on a scale of 0 “never a problem” to 3 “severe problem.” Higher scores indicate greater problems. This study will utilize the Irritability subscale as it has been used in previous RUBI trials and is sensitive to change with intervention [16, 21]. The irritability subscale has excellent internal consistency (Cronbach’s alpha > 0.90) [52].

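### The Aim 1 sample size and 80% power are worked out on the ABC-I, a secondary outcome, so the stated power is not established for the primary clinical outcome, the SESBI-R.

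*Protocol article*

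**What the plan says.** Under Clinical outcomes, the protocol article labels the SESBI-R "SESBI-R; primary clinical effectiveness outcome". A few lines later it labels the other scale "ABC)-Irritability Subscale (secondary clinical effectiveness outcome". Table 1 assigns the same roles. Hypothesis 1 and Aim 1 analyses speak only of change in externalizing behavior from baseline to Week 24 and name no instrument.

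Sample size and power sets the Aim 1 inputs. It starts from "Assuming a Type-I error rate of 5% and SD of 6.2", then adds "a conservative within-person correlation in externalizing behavior of r = 0.3", a 10% intraclass correlation and 20% attrition. It concludes that 126 children (84 versus 42) in 42 schools are "needed to detect a difference of at least 3.8 points in the comparison of slopes in ABC-I with 80% power". It converts the 3.8 points to d = 0.62 for change in externalizing behavior and calls that effect clinically meaningful, citing an earlier study.

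On the SESBI-R itself, the article reports reliability only: "The Intensity and Problem scales of the SESBI-R have demonstrated internal consistency coefficients", followed by test–retest correlations. The one SESBI-R threshold is the entry criterion, a total score of at least 101, under Autistic children.

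**The concern.** The sample size is justified on one instrument and the primary hypothesis is to be tested on another. The SD and the target difference are in ABC-I points, and nothing in the article ties either number to the SESBI-R. Replacing the instrument's name in the power sentence would therefore not repair it.

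This is not detail that a condensed article leaves to a fuller document. The article has a complete power section, and that section rests on a secondary outcome. The Discussion goes on to describe the trial as fully powered. For the primary clinical outcome, a reader cannot tell what difference in SESBI-R points the trial was designed to detect, or with what power.

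**Working it through.** **Inputs** (Protocol article, Sample size and power): difference 3.8; SD 6.2; alpha 5%, taken as two-sided because the article does not say; power 80%; allocation 84:42; attrition 20%; intraclass correlation 0.10; 3 dyads per school; within-person correlation 0.3.

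**Step 1: reproduce the plan's figure on the ABC-I.**

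Standardized effect: 3.8/6.2 = 0.613, stated as 0.62.

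Control-arm size at 2:1 allocation: n = 1.5 × SD² × DE × (1.960 + 0.842)² / 3.8², where DE is the variance inflation. Total evaluable = 3n; total enrolled = 3n/0.8.

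- DE = 1.1 (10% inflation), no use of the within-person correlation: n = 1.5 × 38.44 × 1.1 × 7.849 / 14.44 = 34.5. That is 103.4 evaluable and 129.3 enrolled, against 126 stated. At 126 enrolled, power is 79.0% and the detectable difference is 3.85 points.
- DE = 1 + (3 − 1) × 0.10 = 1.2, with variance reduced by baseline adjustment (1 − 0.3² = 0.91): 128.3 enrolled, power 79.3%, detectable difference 3.84 points.

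Both come within 3% of 126, so the ABC-I arithmetic is reproducible. Two less favourable readings do not match. DE = 1.2 without the 0.91 factor gives 141 children and 75.4% power at 126. A change-score SD of 6.2 × √(2 × 0.7) with DE = 1.2 gives 197 children and 61.0% power at 126.

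**Step 2: what the design gives for any outcome, in standardized units.**

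Evaluable children: 84 × 0.8 = 67.2 and 42 × 0.8 = 33.6. SE of d = √[DE × (1/33.6 + 1/67.2)] = √(DE × 0.04464).

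- DE = 1.1: SE = 0.2216; detectable d at 80% power = 2.802 × 0.2216 = 0.62.
- DE = 1.2: SE = 0.2315; detectable d = 2.802 × 0.2315 = 0.65.

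Power for other true effects is Φ(d/SE − 1.960):

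| True d | DE = 1.2 | DE = 1.1 |
|---|---|---|
| 0.5 | 58% | 62% |
| 0.4 | 41% | 44% |
| 0.3 | 25% | 27% |

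**Step 3: try the same for the SESBI-R.** This cannot be done from the article, which gives no SESBI-R SD, target difference or correlation. Purely as an illustration, for an assumed SD between 20 and 50 points the detectable difference would run from 0.62 × 20 = 12 to 0.65 × 50 = 32 points. That range is an assumption, not a figure from the documents.

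**The case against.** The strongest reply is that power does not depend on the units of the scale. The article restates the effect as d = 0.62 for change in externalizing behavior, which is the construct of Hypothesis 1, and it attaches clinical meaningfulness to that effect size. If the SESBI-R had the same standardized effect, correlation, clustering and attrition, 126 children would give about the same power. Earlier RUBI work used the ABC-I, which may be why the planning inputs are on that scale.

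Much of this stands. A unit-free planned effect exists, so it would be wrong to say that nothing can carry over or that a null SESBI-R result could be read against no planned effect at all. But the transfer is neither stated nor justified, and the article gives reasons not to take it for granted:

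- It describes the ABC-I as responsive to intervention and says no such thing of the SESBI-R.
- In the measures section, the source cited for clinical meaningfulness supports the ABC-I and the CGI-I, not the SESBI-R.
- The SESBI-R is part of the entry criterion and the ABC-I is not. Selection on a score can alter its baseline spread and its correlation with follow-up.

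A reader might also set SESBI-R points beside the 3.8 ABC-I points and conclude that sensitivity is lost. That compares two scales and shows nothing: each figure is the same d multiplied by a different SD.

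The article does not say which SESBI-R scale is analysed, but this is a lesser matter. The Problem items are yes/no, and 38 of them scored 0/1 cannot reach 101, so the entry cutoff points to the frequency (Intensity) score. That is an inference from an eligibility rule, and a condensed article may leave the detail elsewhere.

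**Conclusion.** The point holds: the power section and the primary outcome refer to different instruments, and 80% power is not established for the SESBI-R. The fault lies in the outcome to which the calculation was applied, not in its arithmetic.

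A reader might infer that Aim 1 is underpowered. The documents do not support that, because they contain no SESBI-R inputs from which to judge it. What can be said is conditional: the design detects about d = 0.62 to 0.65 with 80% power, and has about 58 to 62% power if the true SESBI-R effect is d = 0.5. These figures assume a two-sided 5% test, a variance inflation of 1.1 to 1.2, 20% attrition, a normal approximation, and an SD that already describes the analysed quantity.

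**What to change.** Keep 126 children in 42 schools, and do one of the following:

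1. Restate the Aim 1 calculation for the SESBI-R. Name the scale analysed (the cutoff of 101 suggests Intensity), take the SD and within-person correlation from any justified source, and give the detectable difference in SESBI-R points with its power. The article does not say that the RUBIES pilot collected the SESBI-R, so the source need not be the pilot.
2. State that d = 0.62 is being applied to the SESBI-R, and justify it.
3. Reconcile which instrument is primary across Clinical outcomes, Table 1 and Sample size and power.

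Under options 1 and 2, keep 3.8/6.2 only as the power statement for the secondary ABC-I.

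The cost is a rewritten paragraph and a sourced SESBI-R SD and correlation, with no extra participants. The article reports no enrolment as of February 2026, so the change can be made before any data exist. The downside is that the stated power or detectable difference may turn out less favourable.

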#### Implementation outcomes

Sustainment (primary implementation outcome) is defined as the level of educator fidelity to RUBIES through the second year of study enrollment (Weeks 52 and 76). Fidelity to RUBIES is operationalized on the RUBIES Educator Behavior Support Plan Implementation (BSPI) measure which will be rated by a trained independent evaluator masked to study condition. The BSPI is designed to assesses the educator’s current implementation of strategies that are detailed on the Behavior Support Plan, which is an organizing document that captures all RUBIES strategies developed for the educator’s student in collaboration with the RUBIES coach and implemented by the educator in Year 1. The IE rating on the BSPI will be completed at Weeks 16, 24, 52, and 76 and will be based on discussion with the educator around their current implementation of RUBIES strategies documented on their behavior support plan. Ratings on the BSPI are based on a scale of 1–8 (1 “none of the components of the behavior support plan are being implemented”; 4 “behavior support plan is partially implemented and with some implementation errors”; 8 “the behavior support plan is implemented consistently as intended in its entirety”). In a prior study of RUBIES, BSPI scores of educators randomized to RUBIES averaged 6.78 (SD = 1.25; scale of 1–8) [21].

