### Aim 2 analyses

Aim 2 compares the effect of HELM vs. educator coaching on RUBIES sustainment as measured by BSPI scores (arm 1 vs. arm 2). The hypothesis states that intervening with HELM will induce better sustainment (i.e., higher RUBIES fidelity) in Year 2 at Week 52 and Week 76 compared to educator coaching only. The two observations of sustainment for each educator (paired 1:1 with a child) in Year 2 are nested within the educator, who is nested within a school. For this outcome, we will fit an LMM with the following hierarchical structure: the Level 1 model (observation) will include Week 52 and Week 76 fidelity observations for each educator. This level does not include a growth model because we do not assume fidelity will systematically increase or decrease during the sustainment school year; instead, we assume random fluctuation around an educator mean for the year. At Level 2 (educator), we will include a random intercept and educator-level covariates such as years of experience which may be a potential confounder. Covariates will be selected as described above. At Level 3 (school), we will include a random intercept and a treatment assignment indicator (RUBIES + HELM vs. RUBIES only) which will be contrast coded to facilitate main effect interpretations. The coefficient for the treatment assignment indicator in this model will test whether RUBIES sustainment (i.e., level of RUBIES fidelity in the second year of study enrollment) was superior for educators assigned to RUBIES + HELM compared to educators assigned to RUBIES only at Week 52 and Week 76. As a secondary implementation outcome, we will analyze a binary indicator of RUBIES sustainment at Week 52 and Week 76 (based on the CGI-S) to evaluate whether HELM improved the odds of sustaining RUBIES at a provisional ‘sustainment’ cutoff. This analysis will use a similar model as Aim 2, but data from different timepoints or distributions (LMM and Generalized LMM for binary outcomes).

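### The Aim 2 power statement gives a detectable difference of 0.13 with SD 0.17, which is not in units of the 1–8 BSPI; at d = 0.76 and SD 1.25 the difference is about 0.95 points, and the second Year 2 rating appears unused

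*Protocol article*

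**What the plan says.** The Aim 2 analyses section of the protocol article makes the outcome "RUBIES sustainment as measured by BSPI scores (arm 1 vs. arm 2"). The model takes the Week 52 and Week 76 ratings of each educator, with random intercepts for educator and school and no growth term.

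The Implementation outcomes section fixes the scale: "Ratings on the BSPI are based on a scale of 1–8". It also gives the only BSPI mean and spread in the article, from a prior RUBIES study: "BSPI scores of educators randomized to RUBIES averaged 6.78 (SD = 1.25; scale of 1–8").

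The Sample size and power section puts the Aim 2 result as "we have 80% power to detect a difference of at least 0.13 (or d = 0.76) in RUBIES sustainment". The spread enters as "assuming SD = 0.17 based on pilot RUBIES data". The sample behind it is 42 educators per arm in 28 schools. Further inputs are a within-person correlation of 0.3, attrition of 25%, and "a Type-I error rate of 0.05, 10% variance inflation for clustering within school effect". Nowhere does the section name the instrument or scale behind 0.17 and 0.13.

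**The concern.** The article gives two SDs for what reads as one outcome, 1.25 and 0.17, and does not reconcile them. They differ by a factor of 1.25/0.17 = 7.35. On a rating from 1 to 8, an SD of 0.17 would mean that educators hardly differ from one another.

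A reader who takes 0.13 as BSPI points would think the trial can resolve a very small difference in fidelity. What it can detect at 80% power is somewhere between three quarters of a point and a full point. Nobody can judge whether such an effect of HELM is plausible or worthwhile until it is given on the scale on which it will be measured.

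There is a second, separate question. The statement lists a correlation between repeated ratings, and the planned analysis uses two ratings per educator, so the stated result should reflect both.

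**Working it through.** **Inputs.** From Sample size and power: 42 educators per arm, 25% attrition, 10% for clustering, within-person r = 0.3, alpha 0.05, 80% power, SD 0.17, difference 0.13, and the expected cluster size ("We expect 3 child-educator dyads per school to consent and enroll in the study"). From Implementation outcomes: BSPI SD 1.25. Assumed here: two-sided alpha and a normal approximation. The 10% is read either as an intraclass correlation of 0.10 or as a direct 10% variance inflation.

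**Step 1. Standardized effect.** 0.13/0.17 = 0.765, which agrees with the stated 0.76.

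**Step 2. Reproduce the 80% with one rating per educator.** Educators per arm after attrition: 42 × 0.75 = 31.5. Effective number per arm: n = 31.5/DE. Detectable d = (1.960 + 0.842) × √(2/n). The power column uses d = 0.13/0.17.

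| Design effect (DE) | n per arm | Power | Detectable d | × 0.17 | × 1.25 (BSPI points) |
|---|---|---|---|---|---|
| 1 + (3 − 1) × 0.10 = 1.2 | 26.25 | 79.1% | 0.773 | 0.131 | 0.97 |
| 1 + (2.25 − 1) × 0.10 = 1.125 (2.25 educators per school after attrition) | 28.0 | 81.6% | 0.749 | 0.127 | 0.94 |
| 1.1 (direct inflation) | 28.6 | 82.5% | 0.740 | 0.126 | 0.93 |

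The stated 80% at d = 0.76 reproduces to within about 2 points in the first two rows.

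**Step 3. The same effect on the BSPI.** 0.76 × 1.25 = 0.95 points (0.96 with the unrounded 0.765).

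**Step 4. Use both Year 2 ratings.** The mean of two ratings with correlation 0.3 has variance factor (1 + 0.3)/2 = 0.65. With DE 1.2, n = 26.25/0.65 = 40.4 per arm. Detectable d = 2.802 × √(2/40.4) = 0.62, which is 0.62 × 1.25 = 0.78 BSPI points. Power at d = 0.76 is about 93%. With DE 1.1 the figures are 0.60 and 0.75 points.

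Multiplying 0.65 by 1.2 is a simplification. Suppose instead that the 10% is the school share of the variance of a single rating, and the correlation of 0.3 includes it. The components are then 0.10 (school), 0.20 (educator) and 0.70 (residual). The variance factor per educator becomes 3 × 0.10 + 0.20 + 0.70/2 = 0.85 instead of 0.78. Then n = 31.5/0.85 = 37.1, detectable d is 0.65 (0.81 points), and power at d = 0.76 is about 91%. The conclusion is the same.

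**Step 5. Other routes to 0.76.** A change score between two ratings has variance factor 2 × (1 − 0.3) = 1.4. With no attrition and DE 1.1, n = 42/(1.1 × 1.4) = 27.3, and detectable d is also 0.76. That route leaves out the listed attrition and tests a change, whereas Aim 2 compares the Year 2 level. With 25% attrition included, it gives a detectable d of 0.88. So how 0.76 was obtained cannot be settled from the article, but averaging the two ratings under all the listed assumptions does not produce it.

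**Step 6. Possible origin of 0.17.** 1.25/7 = 0.179 and 1.25/8 = 0.156, so 0.17 would fit a BSPI rescaled to run from 0 to 1, or a proportion-type fidelity score. The article states neither.

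**The case against.** The strongest reply is that nothing in the design fails. The same sentence gives d = 0.76, which does not depend on units, and it reproduces. If 0.17 and 0.13 come from a rescaled or proportion-type score, they are unlabelled rather than wrong. If both ratings are used, the trial has more standardized power than it claims. All of this stands, and it confines the point to the raw figures and the description of the inputs. It does not remove the point: the article names no second scale, and a standardized effect can be judged only against the SD of the outcome it refers to.

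A reader might go further in three ways that the article does not support.

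- **That the detectable effect is understated seven-fold, or that true power is about 7%.** The factor of 7.35 applies only to the raw difference. Power of about 7% results only if 0.13 is taken as BSPI points at SD 1.25 and the adjacent d = 0.76 is ignored.
- **That arm 1 would have to average 6.78 + 0.95 = 7.73, close to the ceiling of 8.** This assumes that arm 2 stays at 6.78 in Year 2. That mean comes from a prior study, with no time point given, and the article's own rationale is that fidelity drops between school years.
- **That a null Aim 2 result would be uninformative.** This rests on the same ceiling assumption and does not follow.

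It is also not stated that the prior study with SD 1.25 and the pilot data with SD 0.17 are the same source, so they should not be treated as one.

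**Conclusion.** The point holds in a limited form. The raw figures in the Aim 2 power statement are not in units of the stated primary implementation outcome, and no other scale is named. At the stated d, the BSPI difference is about 0.95 points, not 0.13. At 80% power it is 0.93 to 0.97 points with one rating and about 0.78 with two (0.75 to 0.81 across the readings of the clustering and correlation inputs). The sample size and the claim of about 80% power at d = 0.76 are not undermined; with both ratings, power at that effect is about 93%.

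The BSPI figures assume that SD 1.25 applies to each Year 2 rating, which the article does not say, and they scale in proportion to that SD. That the second rating went unused is inferred by back-calculation. What is firm is that averaging the two ratings under the listed assumptions does not give the stated result.

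**What to change.** Restate the Aim 2 detectable difference in BSPI points. Give the SD assumed for Year 2 and its source (for example 1.25 from the prior study), the design effect and whether the 10% is an intraclass correlation or a direct inflation, the 25% attrition, and whether one or two ratings are used.

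With SD 1.25 and DE 1.2, this gives about 0.97 points for one rating (0.95 if d = 0.76 is kept) and about 0.78 points (d about 0.62) for the mean of two at r = 0.3. If one rating is the intended basis, drop r = 0.3 from the list or say that the second rating is held as a margin. Remove 0.13 and 0.17, or name the measure and scale they belong to and show how that measure relates to the BSPI.

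The cost is a few lines in the sample-size section. Enrolment targets, outcome and model stay as they are, and the article reports that no participants had been enrolled as of February 2026. The raw detectable difference will look larger than 0.13; the standardized one stays at 0.76 or falls to about 0.62.

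### The Aim 2 power statement (80% power at d = 0.76) does not follow from its listed inputs for the planned two-visit analysis, which give a detectable effect of about d = 0.60 to 0.65

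*Protocol article*

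**What the plan says.** The Aim 2 paragraph of Sample size and power claims "80% power to detect a difference of at least 0.13 (or d = 0.76) in RUBIES sustainment (Week 52 and Week 76", closing the parenthesis after the two visits. Its inputs are:

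- **Sample:** "With 84 educators as the effective sample size (42 each), nested within 28 schools".
- **SD:** "assuming SD = 0.17 based on pilot RUBIES data".
- **Alpha:** "a Type-I error rate of 0.05", sidedness not stated.
- **Clustering:** "10% variance inflation for clustering within school effect".
- **Attrition:** 25% of educators.
- **Repeated ratings:** "within-person correlation of observations = 0.3".

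The cluster size comes from the Aim 1 paragraph of the same section: "We expect 3 child-educator dyads per school to consent and enroll in the study".

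The Aim 2 analyses section describes the model as three-level. "The two observations of sustainment for each educator" in Year 2 are nested in the educator, who is nested in the school. There is no growth term, because fidelity is assumed to fluctuate at random around the educator's mean for the year. The treatment coefficient is the test. The Methods part of the Abstract likewise defines the primary implementation outcome as average fidelity over Weeks 52 and 76.

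**The concern.** The outcome is a level averaged over two ratings, and the correlation between those ratings is given as 0.3. Averaging two such ratings reduces the variance to (1 + 0.3)/2 = 0.65 of a single rating's variance. A detectable effect computed from these inputs should therefore be clearly smaller than one computed for a single rating. The stated 0.76 lies where the single-rating figure lies.

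What is at stake is whether the power statement for a primary outcome can be reproduced. As written, a reader cannot tell whether 0.76 describes the two-visit average, a single visit or some other analysis, and the protocol understates what its HELM comparison can detect.

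**Working it through.** **Inputs.** 42 educators per arm × 0.75 = 31.5 per arm after attrition. Two-sided alpha 0.05 is assumed, with 80% power: 1.960 + 0.842 = 2.802. The stated effect is 0.13/0.17 = 0.765, printed as 0.76. The 10% clustering can be read in two ways:

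- a flat variance inflation of 1.10;
- an intraclass correlation of 0.10 with 3 educators per school, giving 1 + 2 × 0.10 = 1.20.

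**Formula.** d = 2.802 × √(2V/31.5), where V is the variance multiplier relative to one independent rating. Power at 0.765 is Φ(0.765/√(2V/31.5) − 1.960).

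**Step 1: reproduce the stated figure.** With one rating per educator and the correlation unused:

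- V = 1.10: d = 2.802 × √(2.20/31.5) = 0.740
- V = 1.20: d = 2.802 × √(2.40/31.5) = 0.773

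These bracket 0.76. At V = 1.20, power at 0.765 is 79.1%. At V = 1.10, using t on 2n − 2 degrees of freedom and rounding down to 31 per arm gives 0.759.

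**Step 2: apply the listed inputs to the planned two-visit mean.** The first two rows multiply the clustering inflation by 0.65. The last two build the variance of a three-level mean with 3 educators per school:

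- If 0.3 is the total within-person correlation, V = (1 + 0.3)/2 + 2 × 0.10 = 0.85.
- If the school component of 0.10 is added to 0.3, V = (1 + 0.4)/2 + 2 × 0.10 = 0.90.

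| Reading | V | d (normal) | d (t, 26 df) | Power at 0.765 (normal) |
|---|---|---|---|---|
| 1.10 × 0.65 | 0.715 | 0.597 | 0.620 | 95% |
| 1.20 × 0.65 | 0.780 | 0.623 | 0.648 | 93% |
| Three-level, total correlation 0.3 | 0.85 | 0.651 | 0.676 | 91% |
| Three-level, 0.10 added to 0.3 | 0.90 | 0.670 | 0.696 | 89% |

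The 26 degrees of freedom are 28 schools minus 2. If attrition thins the schools to 3 × 0.75 = 2.25 educators each, the third row becomes V = 0.65 + 1.25 × 0.10 = 0.775 and d = 0.621.

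On the section's own scale (SD 0.17), d of 0.597 to 0.651 is a difference of about 0.10 to 0.11, against the stated 0.13.

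**Step 3: what correlation would give 0.765?** Solving 0.765 = 2.802 × √(2 × DE × k/31.5) for k = (1 + r)/2:

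- DE = 1.20: k = 0.978, so r ≈ 0.96
- DE = 1.10: k = 1.067, so r ≈ 1.13, which is impossible

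The listed value is 0.3.

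**Step 4: sensitivity to the correlation.** At r = 0.6, k = 0.80. Then d is 0.662 (1.10) or 0.692 (1.20), and 0.688 or 0.719 with 26 df. Doubling the assumed correlation still leaves d below 0.76.

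**The case against.** **The error is conservative and changes nothing in the trial.** This stands. The 84 educators are the arm 1 and arm 2 share of a sample sized for Aim 1, so no Aim 2 sample size was derived from 0.76. A reader might infer from a wrong power statement that the comparison is underpowered. The arithmetic shows the opposite.

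**A null result is read from its estimate and confidence interval, not from a planning figure.** This also stands. The protocol does not make 0.13 a threshold of importance or a decision rule for HELM; its remark on clinical meaning concerns Aim 1. The cost is a misleading benchmark, not a wrong inference.

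**The cause is not established.** A reader might infer that the correlation was simply ignored, because single-rating figures surround 0.76. The protocol does not say so, and 0.740 and 0.773 only bracket the value. Other routes that use 0.3 also come close:

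- A change-score variance of 2(1 − 0.3) = 1.4, with inflation 1.10 and no attrition, gives 0.759.
- A baseline-adjustment factor of 1 − 0.3² = 0.91, with design effect 1.20, gives 0.738, or 0.766 with 26 df.

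Neither fits the Year 2 level model in the Aim 2 analyses section, and the first drops the stated attrition. So the cause stays open, but the mismatch does not depend on it.

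**The SD of 0.17 may already be that of an educator average.** This is possible, since the protocol does not say. No 0.65 factor would then apply, and a correlation of 0.3 would have no role among the inputs. The paragraph would still need correcting.

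**Conversion to BSPI points.** A reader might want to translate the gap using the SD of 1.25 on the 1–8 BSPI scale given under Implementation outcomes. The Aim 2 calculation does not use that SD, so the documents do not support the conversion. How an SD of 0.17 relates to a 1–8 scale is a separate issue. It does not affect a comparison made in units of d.

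**Conclusion.** The concern holds as an inconsistency between a stated figure and its stated inputs. For the two-visit mean that the protocol plans to test, those inputs give a detectable effect of about d = 0.60 to 0.65 by normal approximation. The least favourable variance reading gives 0.67, or about 0.70 with a 26-df correction. Power at d = 0.76 is about 89% to 95% by normal approximation, against the stated 80%.

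This rests on a two-sided 5% test, 31.5 educators per arm after attrition, and 0.17 being the SD of a single rating. Both readings of the 10% clustering lead to the same conclusion. The direction is favourable to the trial, so this is a reporting error in the power statement of a primary outcome, not a design flaw.

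**What to change.** Recompute the Aim 2 figure for the average of Weeks 52 and 76. State three things alongside it:

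- whether the 10% is a flat inflation or an intraclass correlation with 3 educators per school;
- whether the SD of 0.17 belongs to one rating or to the educator average;
- whether a small-number-of-schools correction is used.

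Then restate either the detectable effect at 80% power or the power at d = 0.76, and add a higher within-person correlation (for example 0.6) as a sensitivity value.

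If 0.76 is meant for a single visit, or if 0.17 is already the SD of the average, say so and remove the within-person correlation from the inputs.

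The cost is wording in the Sample size and power section. Sample size, randomization and the Aim 2 model are unaffected, and the Discussion reports no enrolment as of February 2026.
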